## Abstract

**Background:**

A low birth weight is an independent risk factor for adverse infant outcomes and a predictor of chronic disease in adulthood. In these situations, differentiating between prematurity and small for gestational age (SGA) or simultaneous conditions is essential to ensuring adequate care. Such diagnoses, however, depend on reliable pregnancy dating, which can be challenging in developing countries. A new medical optoelectronic device was developed to estimate gestational age (GA) at birth based on newborn skin reflection.

**Objective:**

This study will aim to evaluate the device’s ability to detect prematurity or SGA, or both conditions simultaneously as well as predict short-term pulmonary complications in a cohort of low-birth-weight newborns.

**Methods:**

This study protocol was designed for a multicenter cohort including referral hospitals in Brazil and Mozambique. Newborns weighing 500-2500 g will be eligible for inclusion with the best GA available, considering the limited resources of low-income countries. Comparator-GA is based on reliable last menstrual period dating or ultrasound assessment before 24 weeks’ gestation. Estimated GA at birth (Test-GA) will be calculated by applying a novel optoelectronic device to the newborn’s skin over the sole. The average difference between Test-GA and Comparator-GA will be analyzed, as will the percentage of newborns who are correctly diagnosed as preterm or SGA. In addition, in a nested case–control study, the accuracy of skin reflection in the prediction of prematurity-related respiratory problems will be evaluated. The estimated required sample size is 298 newborns.

**Results:**

Teams of health professionals were trained, and standard operating procedures were developed following the good practice guidelines for the clinical investigation of medical devices for human participants. The first recruitment started in March 2019 in Brazil. Data collection is planned to end in December 2020, and the results should be available in March 2021.

**Conclusions:**

The results of this clinical study have the potential to validate a new device to easily assess postnatal GA, supporting SGA identification when pregnancy dating is unreliable or unknown.

**Trial Registration:**

ReBec: RBR-33rnjf; http://www.ensaiosclinicos.gov.br/rg/RBR-33rnjf/

**International Registered Report Identifier (IRRID):**

DERR1-10.2196/16477

## Introduction

### Background

Low birth weight is associated with short- and long-term mortality and morbidity and is a predictor of chronic diseases in adulthood [1,2]. Small for gestational age (SGA) refers to a newborn with birth weight below the tenth percentile for gestational age (GA) and sex according to the expected standard growth curve [2]. Distinguishing between prematurity and SGA or both conditions in low-birth-weight newborns is critical to ensuring appropriate provision of care and has the potential to save lives [3,4]. Treatment of prematurity usually involves respiratory support and the administration of exogenous surfactant, to increase alveolar surface tension. Besides, most SGA newborns may have suffered from chronic intrauterine hypoxia due to placental oxygen delivery failure, and thus require specific support [5]. The diagnoses of prematurity and SGA depend heavily on a reliable GA estimation [6]. Although easy access to early obstetric ultrasonography has overcome many of the uncertainties related to pregnancy dating based on a woman’s recollection of her last menstrual period [6,7], this practice is not widely available in low- and middle-income countries [8]. Pregnancy dating based on the last menstrual period is affected by memory recall, confusion caused by early pregnancy bleeding interpreted as menstruation, irregular menses, the effect of hormonal contraception and intrauterine devices, maternal chronic disease, and poor nutrition [9,10]. Apart from this, unequal access to technological solutions in health care challenges the agenda of sustainable development goals [11] and contributes to increased neonatal morbidity and mortality. The availability of an affordable and low-maintenance device that can accurately evaluate GA at birth has the potential to rationalize management decisions and avoid unnecessary interventions and their related costs, essential aspects of health care systems [12].

### Prior Work

The optical properties of the skin’s interaction with light can be evaluated by devices that emit and receive photons [13]. Variations in light scattering through the skin are believed to be associated with changes in skin thickness, the concentration of chromophores, and light wavelength [14]. A novel technology was developed to estimate GA at birth (Test-GA) by analyzing the photobiological properties of the newborn’s skin in combination with clinical variables [15]. This noninvasive and nonionizing technology features a probe containing light emitters and receivers that is brought in contact with the skin over the sole. A mathematical algorithm provides an estimated GA within seconds, combining the skin reflection with clinical adjusters, such as birth weight and incubator stay [15].

The timeline of the new medical device development involves sequential steps [16], represented in Figure 1. The prototype of the device previously evaluated 115 newborns at 24-41 weeks’ gestation with promising results [15]. After insights from this first clinical experiment published in 2017, the technology received improvements to mitigate external influences in the test, such as humidity, ambient light, and to ease the user handling. The current version is a small device, about the size of a pen, with an automated ability to measure skin reflection. To reduce examiner influence, the device now warns about errors of measurement. Clinical variables are presented in a digital screen immediately after the newborn skin assessment. Since February 2019, a clinical trial is taking place in 5 Brazilian hospitals to advance the GA prediction modeling, using a sample of 787 newborns [17]. The planned date of last enrollment is July 2020.

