### Present Protocol of Research

This protocol gathers data from Brazil and Mozambique referral centers. This step represents the clinical validation of the prediction model established in the preceding clinical trials. It aims to validate an optimized version of the device in low-resource birth settings, using a data set obtained in different populations, before introducing it in the market. The analysis relies on real-world antenatal GA estimations obtained during pregnancy in which first-trimester ultrasound may not always be available or reliable. The primary hypothesis of this study is that photobiological properties of the skin measured by the device, and adjusted by clinical variables, will allow the accurate prediction of GA (Test-GA) in low-birth-weight newborns.

The primary objective of this study is to validate the preemie test statistical model for GA estimation at birth and its accuracy to detect prematurity in low-birth-weight newborns. The secondary objective is to evaluate whether there is an association between skin reflection and the occurrence of early respiratory complications.

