### Data Definition and Collection

Comparator-GA is calculated by obstetric data obtained at the time of enrollment. The requirements for establishing the best GA calculation (assessed by interviewing the mother) are based on the following:

reliable last menstrual period dating, including certainty about last menstrual dating, regular menstrual cycles, no contraceptives within 3 months of conception, and no abortion or delivery 2 months prior to conception [18]; ORultrasound <24 weeks’ gestation, considered reference for low-income countries as recommended by the World Health Organization (WHO) [8], even if the clinical information on last menstrual period is absent.

For data curation, pregnancy dating based on ultrasonography reports will be adjusted to Intergrowth 21 standards. Fetal crown–rump length [23] as well as femur length and head circumference will be used to recalculate GA [24]. When both ultrasound and reliable last menstrual period dating are available, correction will depend on whether there are discrepancies in excess of 5, 7, 10, or 14 days according to the identified GA at first assessment as recommended in ACOG Committee Opinion guideline number 700 (May 2017) [6].

Test-GA will be determined by statistical analysis according to signals stored in the device’s processor and clinical data. For this, the GA modeling prediction is based on the result of another ongoing clinical trial (registration number RBR-3f5bm5). This study is taking place at 5 Brazilian centers with the analysis of the skin reflection and clinical data of 787 newborns, with 24-42 weeks of gestation, using strict rules of the crown–rump length ultrasound measurement for pregnancy dating [17]. We expect to establish the prediction model toward the end of the RBR-3f5bm5 clinical trial in September 2020.

Birth weight is the first measurement performed by the local staff during the first 24 hours of life. A digital scale for standardizing weighing is already present in all settings.

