### Study Outcomes

#### Primary Outcomes

The primary endpoints will be differences between the Test-GA and Comparator-GA estimates and proportion of correct preterm newborn detections by the Test-GA at <37 weeks’ gestation with a 1-week margin of error.

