### Statistical Analysis

To assess differences between the Test-GA and Comparator-GA estimates, average difference (with standard deviations), intraclass correlation coefficient, paired *t*-testing, and Bland–Altman scatter plots [30] will be used. To evaluate the accuracy of Test-GA in identifying preterm and SGA neonates, sensitivity, specificity (with 95% confidence intervals), and receiver operating characteristic curves and other discriminant analysis techniques will be calculated. The relationship between the measurement of the newborn’s skin reflectance and newborn’s respiratory complications due to immaturity will be evaluated using receiver operating characteristic curves, association tests, and risk ratios. The significance level for hypothesis tests will be 5%, together with 95% confidence intervals.

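### Test-GA already contains birth weight, and no planned analysis shows how much of its accuracy comes from the skin signal

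*Protocol article*

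**What the plan says.** **What Test-GA is.** The protocol article (Introduction, Prior Work) describes an algorithm "combining the skin reflection with clinical adjusters, such as birth weight and incubator stay". Data Definition and Collection confirms this for the present study: "Test-GA will be determined by statistical analysis according to signals stored in the device’s processor and clinical data". The model itself comes from the development trial RBR-3f5bm5 and was expected in September 2020. The same section says that a digital scale is available at every site.

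**What is hypothesised.** Under Present Protocol of Research, the primary hypothesis is that "photobiological properties of the skin measured by the device, and adjusted by clinical variables, will allow the accurate prediction of GA" in low-birth-weight newborns. The primary objective is to "validate the preemie test statistical model for GA estimation at birth and its accuracy to detect prematurity in low-birth-weight newborns".

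**What is analysed.** The primary endpoints are "differences between the Test-GA and Comparator-GA estimates and proportion of correct preterm newborn detections by the Test-GA". Statistical Analysis lists, for agreement, "average difference (with standard deviations), intraclass correlation coefficient", a paired t-test and Bland-Altman plots. "To evaluate the accuracy of Test-GA in identifying preterm and SGA neonates", it lists sensitivity, specificity, ROC curves and further unspecified discriminant techniques. All of these use the composite. Skin reflectance by itself is analysed only against respiratory complications.

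**The concern.** Birth weight tracks gestational age and costs nothing extra where a scale is already in use. If Test-GA agrees well with Comparator-GA, the listed analyses leave open whether the probe or the scale did the work. The question matters because the study is the validation step before the device is put on the market. A hospital deciding whether to acquire the probe needs to know what it adds to information already held. Without a model that lacks the skin signal, applied to the same newborns, a good composite result has no baseline to be read against.

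**Working it through.** **1. What the planned sample size covers.** The article gives 298 newborns, an accuracy range of 90%-100%, and use of the lower value.
- Rule tried: the smallest n at which the one-sided 95% exact binomial lower limit is at least L with probability 0.95.
- Inputs: L = 0.90 (stated lower value) and expected accuracy 0.95 (assumed midpoint of the stated range).
- Result: n = 298, an exact match. At n = 298, at least 277 correct results are needed. The probability of that is 0.049 if true accuracy is 0.90 and 0.954 if it is 0.95.
- On this reading, 298 is an accuracy calculation for Test-GA alone, with no term for a comparison against a model without the skin signal.

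**2. Which analysis isolates the skin signal?**

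| Question | What is scored | Model without skin signal? |
|---|---|---|
| Difference in GA | Test-GA vs Comparator-GA | No |
| Preterm (<37 weeks) | Test-GA vs Comparator-GA | No |
| SGA | Test-GA vs Comparator-GA | No |
| Respiratory complications (nested study) | Skin reflectance and Test-GA | No; controls paired in three broad birth-weight bands |

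The last row addresses a different outcome and does not answer the gestational-age question.

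**3. How good could birth weight alone look? (illustration)** The documents give none of these inputs, so all are assumed: 35% preterm births in the source population, a coefficient of variation (CV) of birth weight at given GA of 12%, 15% or 18%, and a model fitted in all births and then applied to 500-2499 g. A skin signal with a 2-week error is shown beside it.

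| CV | Model | Mean diff. (wk) | SD (wk) | ICC | Sensitivity | Specificity | AUC |
|---|---|---|---|---|---|---|---|
| 12% | weight only | 0.19 | 1.44 | 0.88 | 100% | 0% | 0.86 |
| 12% | weight + skin | 0.13 | 1.17 | 0.92 | 99% | 33% | 0.95 |
| 15% | weight only | 0.14 | 1.79 | 0.83 | 100% | 0% | 0.84 |
| 15% | weight + skin | 0.09 | 1.34 | 0.91 | 98% | 48% | 0.95 |
| 18% | weight only | 0.07 | 2.09 | 0.78 | 100% | 0% | 0.81 |
| 18% | weight + skin | 0.04 | 1.47 | 0.90 | 97% | 57% | 0.95 |

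Overall accuracy = prevalence × sensitivity + (1 − prevalence) × specificity. The simulated preterm prevalence within 500-2499 g is about 0.94, 0.88 and 0.82.
- Weight only: 0.937 × 1 + 0.063 × 0 = 93.7%; likewise 87.6% and 81.7%.
- Weight + skin at CV 12%: 0.937 × 0.991 + 0.063 × 0.332 = 94.9%; likewise 91.9% at CV 15% (0.876 × 0.981 + 0.124 × 0.484) and 89.7% at CV 18% (0.816 × 0.970 + 0.184 × 0.573).

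In the first scenario, weight alone passes the 90% lower value simply by calling every infant preterm. Other assumed inputs move the figures. With 12% or 35% preterm births at source, weight-only sensitivity runs from 80% to 100% and overall accuracy from 70% to 93%. The weight-only baseline therefore has to be measured in the study's own newborns.

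**4. Can 298 newborns carry the comparison?** For one added predictor at two-sided 5% and 80% power, the required noncentrality is about 7.85. So f² = 7.85/298 = 0.0263, a partial R² of 0.0263/1.0263 = 0.026. A small contribution to GA prediction is detectable. Specificity is different. Under the assumed prevalences, the number of term infants is 298 × 0.063 = 19, 298 × 0.124 = 37, or 298 × 0.183 = 55.

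**The case against.** A reader might infer that the study fails to test its own primary hypothesis. The text does not support that. The hypothesis names skin properties adjusted by clinical variables, and the quantity it predicts is Test-GA, the composite. The primary objective is to validate the model. Test-GA against Comparator-GA tests this directly, and nothing in the article hypothesises that skin beats birth weight.

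A second tempting reading is that a useless sensor would pass unnoticed. That is too strong. Specificity and ROC curves are planned, and in the illustration the weight-only model does badly on specificity and gives an AUC well below 0.95. The SGA endpoint helps too: a GA built from weight alone gives every same-sex infant of the same weight the same SGA label, so poor SGA accuracy would hint at a weight-driven model. These are indirect signs, however. They do not measure the sensor's share, and other clinical variables such as incubator stay could also improve them.

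The figures rest on assumptions outside the documents and vary with them. That limits the stated size but not the structural point.

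Finally, this is a condensed article, an unseen analysis plan might contain the benchmark, and predictor selection belongs to the development trial. This is a fair reason to treat the point as an improvement rather than an error. Still, the article lists its analyses specifically, and a general mention of other discriminant techniques does not name such a comparison.

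**Conclusion.** The point holds in a limited form. The planned analyses can validate the composite and so meet the primary objective. They cannot, as listed, apportion its accuracy between skin reflection and the clinical variables. That birth weight enters the final model rests on the described algorithm and the reference to clinical data, since the model was not yet established.

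The size is illustrative only. Under the assumed inputs, weight alone can give a near-zero mean difference, an ICC of about 0.8-0.9 and high preterm sensitivity, with poor specificity and an AUC of about 0.81-0.86. The limit applies to the plan as written, not to the data: device signals and clinical data are both stored, so the comparison can be added. It is a low-cost improvement that bears on what may be claimed for the device. It does not invalidate the primary result.

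**What to change.** When the RBR-3f5bm5 prediction model is locked, also lock a reference model from the same development data, with the same clinical variables and no skin signal. Apply both to the same validation newborns. As a prespecified secondary analysis, report with 95% confidence intervals:
- the paired difference in absolute GA error;
- the paired difference in AUC for <37 weeks;
- the paired differences in sensitivity and specificity, noting that the specificity comparison may be imprecise because the number of term infants is not fixed.

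Leave the primary accuracy endpoints unchanged, and do not make superiority over the reference model a condition for the primary hypothesis. State that accuracy will be attributed to skin reflection only if this comparison supports it.

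Cost: one extra model and access to the development trial's data, with no new participants or procedures. The device claim may become more modest if the skin signal adds little.

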**Figure 1 figure1:**
[figure not shown]
The development timeline of the preemie-test device. GA: gestational age.

### Present Protocol of Research

This protocol gathers data from Brazil and Mozambique referral centers. This step represents the clinical validation of the prediction model established in the preceding clinical trials. It aims to validate an optimized version of the device in low-resource birth settings, using a data set obtained in different populations, before introducing it in the market. The analysis relies on real-world antenatal GA estimations obtained during pregnancy in which first-trimester ultrasound may not always be available or reliable. The primary hypothesis of this study is that photobiological properties of the skin measured by the device, and adjusted by clinical variables, will allow the accurate prediction of GA (Test-GA) in low-birth-weight newborns.

The primary objective of this study is to validate the preemie test statistical model for GA estimation at birth and its accuracy to detect prematurity in low-birth-weight newborns. The secondary objective is to evaluate whether there is an association between skin reflection and the occurrence of early respiratory complications.

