## Results

The study began in November 2018 with the training of health professionals in the different participating centers. Then, standard operating procedures were developed following the good practice guidelines for the clinical investigation of medical devices for human participants. The first recruitment started in March 2019 in Brazil. Data collection is planned to end in December 2020, and the results should be available in March 2021.

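### The model called established is still being developed in Brazilian newborns during this study's recruitment, and the printed text neither separates the two samples nor provides for a Mozambique-specific result

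*Protocol article*

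**What the plan says.** All references are to the Protocol article.

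- Present Protocol of Research, on the status of the model: "This step represents the clinical validation of the prediction model established in the preceding clinical trials". The next sentence gives the aim: "It aims to validate an optimized version of the device in low-resource birth settings, using a data set obtained in different populations", before the device goes to market.
- Prior Work, on where the model comes from: "Since February 2019, a clinical trial is taking place in 5 Brazilian hospitals to advance the GA prediction modeling". Last enrolment in that trial is planned for July 2020. The five hospitals are not named.
- Data Definition and Collection describes that trial (RBR-3f5bm5) as ongoing and as analysing "skin reflection and clinical data of 787 newborns, with 24-42 weeks of gestation", dated by crown–rump length. On timing it says: "We expect to establish the prediction model toward the end of the RBR-3f5bm5 clinical trial in September 2020". Test-GA will be worked out from stored device signals and clinical data.
- Results, on this study: "The first recruitment started in March 2019 in Brazil". Data collection is to end in December 2020.
- Study Settings names two Brazilian hospitals and Maputo in Mozambique.
- Eligibility Criteria and Table 1 list the inclusion and exclusion criteria. Enrolment is sequential until the total is reached.
- Sample Size gives one overall figure, 298. Statistical Analysis gives one set of agreement and accuracy measures. Neither mentions country.

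**The concern.** A validation study earns its name from two things: the model is fixed before it meets the validation outcomes, and the validation newborns played no part in fitting it. A claim of validity in other populations also needs a result from a population that the model was not built on.

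The article's description of its own study promises all of this, but its dates and criteria do not secure it. The model is neither established nor preceding. Development and validation recruit in the same country over nearly the same months. Nothing in the printed criteria keeps the two sets of newborns apart. The one country clearly outside the development data has no stated minimum number and no stated estimate of its own.

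If a newborn did enter both data sets, the accuracy figure would be partly in-sample and tend to be optimistic. If Mozambique contributed few newborns, or were visible only inside a combined figure, the result could not support the claim about different populations. The primary objective is to validate the model, and this is the last step described before marketing.

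**Working it through.** **1. Status of the model.** Present Protocol of Research has it established in preceding trials. Prior Work and Data Definition and Collection have it coming from a trial still enrolling, with the model expected in September 2020. Both descriptions cannot be right for the same model, and Test-GA is explicitly tied to the second.

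**2. Calendar, in whole months, both ends included.**
- Development enrolment: February 2019 to July 2020 = 18 months.
- This study: March 2019 to December 2020 = 22 months.
- Overlap: March 2019 to July 2020 = 17 months, which is 17/18 = 94% of development enrolment and 17/22 = 77% of this study's period.
- September 2020 is month 19 of 22, so 18/22 = 82% of the calendar period passes before the model is due.

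These are shares of time, not of newborns. Accrual by month is not given.

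**3. Could one newborn satisfy both studies as printed?** RBR-3f5bm5 takes newborns of 24–42 weeks with crown–rump length dating. This study takes liveborns of 500–2499 g, tested within 24 hours, with a qualified menstrual date or an ultrasound before 24 weeks, and excludes only listed skin-related conditions. A development newborn in that weight range and without those conditions has a qualifying ultrasound and meets no exclusion criterion. At any hospital taking part in both trials, the criteria admit that newborn. Whether any hospital does take part in both cannot be read from the article.

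**4. Order of model and outcomes.** Comparator-GA is obtained at enrolment, and Test-GA is calculated later from stored signals. Most of the reference values could therefore exist before the model does. The blinding described under Intervention hides values from device users at acquisition. It does not cover the people fitting the model.

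**5. What the total of 298 covers.** The plan's figure can be reproduced. It is the smallest n for which a one-sided exact 95% lower limit exceeds 0.90 with probability at least 0.95, if true accuracy is 0.95. The 0.90 is the article's lower value. The 0.95 is assumed, as the midpoint of its 90%–100%. The figure has no country component.

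Sequential enrolment to an overall total leaves the country mix open. Staff in Maputo were trained in July 2019, after Brazilian recruitment had begun in March 2019.

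**6. Precision if Mozambique is read alone.** The split is not stated, so a range is shown. With x correct out of n, the exact 95% limits are Beta(0.025; x, n−x+1) and Beta(0.975; x+1, n−x). At 90% accuracy:
- n = 298 (x = 268): 85.9% to 93.1%
- n = 149 (x = 134): 83.9% to 94.3%
- n = 100 (x = 90): 82.4% to 95.1%
- n = 50 (x = 45): 78.2% to 96.7%

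Sensitivity and specificity use only part of each n, so their intervals are wider.

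**7. How a combined figure can dilute a country-specific bias (mechanism only).** Combined bias = Mozambique's share × its bias, if Brazil has none. With an assumed bias of +1 week, a 30% share gives 0.30 × 1 = +0.3 week and a 50% share gives 0.50 × 1 = +0.5 week. Neither the share nor the bias comes from the article.

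**The case against.** The strongest reply is that the planned order is sound. Signals are stored unseen, the model is due before data collection ends, and results follow in March 2021. Applying a model from a separate sample to stored signals is valid whenever they were recorded. Overlapping calendar time by itself causes no bias. This stands, and a reader who infers from the dates alone that the validation is invalid goes too far.

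A reader might also infer that newborns are shared. The article does not show it. The trials have separate registrations, different dating rules and different birth-weight ranges, and the development hospitals are not named. What remains is narrower: the criteria, which are printed in full, would admit a shared newborn.

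A third inference is that the countries will be pooled. One overall total and one list of analyses make a combined analysis the natural reading, but pooling is never stated, and a condensed article may leave reporting by country, like a model lock, to a fuller document. Silence alone would be no finding. It matters here because the article makes a specific claim about different populations and because the open country mix is a feature of enrolment, which an analysis plan cannot repair afterwards.

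Finally, different populations can be read more widely than country, to include low-resource settings and real-world dating. That is fair, and the Brazilian newborns do add something on those terms. They still do not test transfer to another country. The article's remark that light scattering is thought to vary with chromophore concentration makes that test relevant, without showing that the signal differs by country.

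**Conclusion.** The point holds in a limited form. The contradiction over the model's status is plain, and the 17-month overlap follows from the article's own dates. On the printed text, separation of the samples, a model lock before comparison with Comparator-GA, and a Mozambican result are all unsecured, while the study is described as validation of a finished model in different populations.

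Contamination, pooling and a bias of any given size are not established. The +0.3 and +0.5 week figures show a mechanism under assumed inputs and carry no weight in this conclusion. The month counts rest on planned dates. The intervals assume 90% accuracy and hypothetical country sizes. The claim that only Mozambique lies outside the development data is about country and rests on the development trial being described as wholly Brazilian. The changes are cheap and should be made before the model is applied.

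**What to change.** 1. Reword Present Protocol of Research to say that the model is being developed in RBR-3f5bm5 and will be fixed before it is applied here.
2. Exclude from the validation set any newborn whose data entered RBR-3f5bm5, confirmed by record linkage, and report how many were removed.
3. Lock and date the algorithm and its coefficients before any Test-GA value is compared with Comparator-GA.
4. Report bias, limits of agreement, sensitivity and specificity for Mozambique separately from Brazil, beside any combined estimate. Identify Mozambique as the out-of-country validation and give the number enrolled per country. If enrolment is still open, state the intended country split.

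The cost is a linkage check, a dated record of the lock and extra result columns. A few Brazilian newborns may be lost and, if so, would need replacing to keep 298. Country-specific intervals will be wider than the overall one, to the extent shown in the working.
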